#### Safety evaluation

The safety assessment will include the following: (1) Vital signs (body temperature, heart rate, breathing, and blood pressure) will be measured at each visit. (2) Laboratory tests including routine blood and urine tests, liver and kidney function tests, electrocardiogram (ECG), and other inspections will be performed once at baseline, 24 weeks, and 52 weeks. (3) Adverse events will be evaluated and recorded on the case report form (CRF).

#### Exploratory indicators

The exploratory assessment will include the following: (1) Inflammatory indicators (including but not limited to IFN-γ, IL-6, IL-1β, TNFα, etc.) and lymphocyte classification and count. (2) Microecology of the respiratory tract, mainly to detect the microecological diversity (α diversity, β diversity) and its dominant flora. (3) The infection condition of herpes virus (Herpesvirus, Cytomegalovirus, Epstein-Barr virus). (4) Immunoglobulin (IgA, IgM, IgG).

### Adverse events (AEs)

AEs are any adverse medical events that occur after treatment and are manifested as unexpected symptoms, signs, diseases, or abnormalities in laboratory results. During the trial, AEs are mainly assessed by safety examination and investigator neutral interrogation. AEs are then recorded in detail on CRFs, including the severity, time of onset (time of symptom onset), duration and time of termination, the use of combinations and experimental drugs, effective measures and outcomes, etc. According to the Consensus of Expert on Safety Evaluation of Drug Clinical Trial in Guangdong (Version 2020), determine the causal relationship between the AE and the experimental drug, and divide the correlation evaluation into six levels: definite, probable, possible, possibly irrelevant, to be evaluated and impossible to evaluate.

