### Interventions

All eligible patients will be randomized into two groups as follows:YPF treatment group: YPF 5 g per time, three times daily, for 52 weeks.Control group: placebo 5 g per time, three times daily, for 52 weeks.

YPF and placebo are uniformly supplied by Sinopharm Group Guangdong Medi-World Pharmaceutical Co., Ltd (Foshan, Guangdong Province, China). The experimental drugs, which have an identical appearance and almost similar taste, are manufactured according to the requirements of this clinical trial and meet the relevant quality requirements. YPF granules have been on the market for many years and there are clear standards for prescription, dosage and quality control. Details can be found in the 2020 edition of the Pharmacopoeia of the People’s Republic of China (hereafter referred to as the 2020 Chinese Pharmacopoeia). The placebo formulation consisted mainly of dextrin and mannitol (66.1% and 30.4% of the placebo, respectively). A small amount of 5% YPF extractum (2% of the placebo) was added to make the odour essentially identical to that of YPF. At the same time, a small amount of flavoring agents and food coloring was added to make the taste and appearance of the placebo similar to that of YPF.

Based on the clinical symptoms, signs and the GOLD guideline 2021, all patients in both groups will receive routine therapy (taking the commonly used maintenance medications in COPD, such as ICS/LABA/LAMA, theophylline, roflumilast, etc.) without intervention, but detailed medication should be recorded for summary analysis. At the same time, the medications (or other treatments) that have to be continually taken continuously for the underlying diseases, the dosage, frequency, and duration of use should also be recorded in the case report form (CRF). It’s forbidden to take other Traditional Chinese medicines or proprietary Chinese medicines with the same effect as YPF during the trial.

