#### Safety analyses

All AEs occurring during this study will be listed and the incidence of AEs will be calculated. The χ2 test or Fisher's exact test will be used to compare the incidence of AEs among groups. As for the laboratory indexes, the frequency table and specific situation of changes will be listed.

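### The adverse event definition carries the word 'unexpected', so a literal reading could leave recognised YPF reactions unrecorded and blunt the between-arm safety comparison

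*Protocol article*

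**What the plan says.** Under Adverse events (AEs), the protocol article gives this definition: "AEs are any adverse medical events that occur after treatment and are manifested as unexpected symptoms, signs, diseases, or abnormalities in laboratory results". On how events are found, it says that "AEs are mainly assessed by safety examination and investigator neutral interrogation". The events are then entered on the case report form with severity, timing, measures taken and outcome.

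For causality the same section refers to a 2020 expert consensus from Guangdong and fixes "six levels: definite, probable, possible, possibly irrelevant, to be evaluated and impossible to evaluate".

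Under Safety analyses, "All AEs occurring during this study will be listed and the incidence of AEs will be calculated", and then "The χ2 test or Fisher's exact test will be used to compare the incidence of AEs among groups". Neither sentence restricts the analysis by expectedness or causality.

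Under Interventions, the article notes that "YPF granules have been on the market for many years". It lists no expected reactions to the product and does not define 'unexpected'.

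**The concern.** An AE definition normally captures every untoward event. Whether the event was expected, and whether the drug caused it, are judged afterwards. Here expectedness sits inside the definition, so it can act before anything is recorded.

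This matters more for a marketed product than for a new one, because an investigator may regard its recognised reactions as expected. Those are also the events most likely to differ between YPF and placebo. Safety is a stated aim of this 52-week trial (Abstract; Study design), and eight hospitals will each have to interpret the word. An event that never reaches the case report form cannot be restored by the analysis.

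The causality list raises a smaller issue. It has a firm positive end but no firm negative one, so an event with an evident other cause has no exact code.

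**Working it through.** **1. The definition and the analysis, side by side.**
- The definition joins two conditions with 'and': the event occurs after treatment, and it shows itself as something unexpected. Read literally, 'any' ranges only over events that meet both.
- The Safety analyses section promises to list all AEs. 'AE' there carries the meaning set by the definition, so 'all' cannot bring back an event that the definition left out.
- Neutral questioning governs how events are elicited. The definition still decides which of them are recorded as AEs.

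**2. What other data collection would catch.**
- Exacerbations, hospitalisations with reasons, and the nine-item symptom scale are collected at every follow-up and additional visit (Table 1, Table 2). Exacerbation and admission rates are secondary outcomes.
- Laboratory changes are tabulated separately from AEs (Safety analyses).
- The exposed events are therefore recognised reactions that are not exacerbations, admissions, scale items, vital-sign changes or laboratory findings. The article describes no other field that would hold them. Diary cards are issued, but their content is not given.

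**3. Direction and bounds of the effect.** Notation, for YPF (1) and placebo (0):
- *o* = proportion of patients with at least one AE that is not a recognised reaction
- *e* = proportion whose only AEs are recognised reactions
- *w* = share of those patients left unrecorded, taken as equal in both arms because sites are blinded

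True difference in AE incidence = (o1 − o0) + (e1 − e0)

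Recorded difference = (o1 − o0) + (1 − w)(e1 − e0)

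Difference lost = w(e1 − e0)

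With *w* = 0 (every site records everything) nothing is lost. With *w* = 1 (every site applies the word strictly) the loss is e1 − e0. At 158 per arm, each percentage point of e1 − e0 corresponds to 0.01 × 158 = 1.58 patients. If e1 exceeds e0 and other AEs are balanced, the recorded difference shrinks toward zero. Blinding does not prevent this, because an equal filter still removes a difference that lies in the filtered events. The documents give neither *w* nor the *e* values, so these bounds are as far as the arithmetic goes.

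**4. The causality list.** Six levels are stated and six are printed, so none is missing from the list:
- toward a drug link: definite, probable, possible (3)
- away from it: possibly irrelevant (1)
- no judgement: to be evaluated, impossible to evaluate (2)

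3 + 1 + 2 = 6, and none means unrelated. The specified test uses all AEs whatever their causality code, so this gap does not alter it.

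**The case against.** The best defence is that one loosely chosen word is being given a regulatory meaning that the article never assigns. 'Unintended' is an equally available sense. The sentence begins with 'any', the questioning is neutral, laboratory tests and ECG are scheduled, staff hold GCP training certificates, and all AEs are to be listed. All of this points to full recording. The article is also a condensed account, and operating instructions for AE recording may sit in the full protocol or the case report form guidance.

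Most of this stands, and it rules out several stronger readings:

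- *That expected reactions will go uncounted.* No text tells sites to omit them. Omission is one possible result of a literal reading.
- *That expected worsening of COPD would be lost.* Exacerbations and hospitalisations are collected separately and compared between arms, even if they are not labelled AEs.
- *That the safety comparison is biased.* This would need sites to apply the word strictly and recognised reactions to be more frequent on YPF. The documents establish neither.
- *That related and unrelated events cannot be separated.* The existing scale already allows definite, probable and possible to be grouped against the rest. What is lost is only the distinction between possibly irrelevant and clearly unrelated.
- *That the causality scale is wrong.* The cited consensus is not available here, so its own levels and the intended strength of the fourth level cannot be checked.

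The defence does not remove the ambiguity itself. The definition is printed text, not something the article left out. If 'unintended' was meant, that is a reason to say so.

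**Conclusion.** The point holds as a wording defect with a possible safety consequence. Taken literally, the definition is narrower than its own 'any' and than the promise to list all AEs, and recognised reactions to YPF may go unrecorded as AEs. If they do, and if they are commoner on YPF while other AEs are balanced, the AE incidence comparison moves toward no difference. The loss is between zero and the full between-arm difference in patients whose only AEs are recognised reactions. No figure can be put on it from the documents.

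The missing level for unrelated events is a minor coding point with no effect on the specified comparison. The primary outcome and the sample size are not touched by either issue. The change is worth making because it costs little and unrecorded events cannot be recovered at analysis.

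**What to change.** - In the AE definition, replace 'unexpected' with 'unfavourable or unintended, whether or not expected and whether or not related to the study drug'. The definition then agrees with its opening word and with the Safety analyses section.
- Record expectedness as a separate field on the case report form.
- Check the six causality levels against the cited consensus, and add a level for clearly unrelated events if that source allows it.

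The cost is one sentence, one new field and possibly one new code, with a short note to the sites. The downside is that more AEs will be recorded, so the reported AE incidence will rise in both arms. If recruitment is under way, note the date of the change so that events recorded under the two wordings can be told apart.

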### Quality control and data management

To ensure the successful process of the study and the reliability of the conclusions, the clinical physicians and nurses directly involved in the study all keep a GCP training certificate and are trained in some specific course before the trial. Guangzhou Evidence-Based Medicine Tech Co., Ltd (Guangzhou, Guangdong province, China) as the contract research organization (CRO) is commissioned to make a detailed clinical monitoring plan (CMP) according to the trial. The CMP includes the specific clinical research associate (CRA), frequency, degree, report of the monitoring, etc. The CRA will complete the tasks according to the CMP and the actual progress.

Clinical Trial Electronic Data Capture System (EDC) will be used in this trial and all data will be entered into the EDC system by trained and qualified investigators. If there is any doubt about the data in the EDC system, the data manager will issue an inquiry to the investigator to make sure the data is true and correct. Once the data have been reviewed and verified to be correct, the database is locked by the principal investigator, sponsor statistical analyst, and the data manager. In general, a locked database cannot be unlocked.

### Statistical analysis

The SAS 9.4 statistical software will be used for statistical analysis. Both full analysis set (FAS) and per-protocol set (PPS) will be used for baseline and efficacy analysis, while the safety set (SS) for the safety analysis. Data will be descriptively analyzed and presented as means and standard deviations, medians and interquartile ranges, and frequencies. The minimum, maximum, P25, median, and P75 are given when necessary. All analyses will be two-sided, with a *p*-value of less than 0.05 considered statistically significant.

#### Demographic and baseline analysis

T-test or non-parametric statistical methods will be used for quantitative data according to the distribution of variables. The χ2 test or Fisher's exact probability test will be used for qualitative data, and the Wilcoxon rank-sum test will be used for ranked data.

#### Efficacy analysis

Different analysis methods will be adopted according to the variable type of efficacy indicators. Specifically, Fisher's exact test will be used to compare categorical variables, including the annualized rates of moderate or severe COPD exacerbations, all-cause admission rate, admission rate due to acute exacerbation, the proportion of patients with an SGRQ response, annualized rates of acute exacerbation of COPD with different severity, and the frequency of first-aid drug use. The duration and interval of AECOPD will be tested by the log-rank test, and the Cox proportional-hazards model will be used to calculate the hazard ratio (HR) and 95% confidence interval (CI). The changes in the CAT score, the SGRQ score, the clinical symptom score, and the single clinical symptom score will also use the log-rank test and the Cox proportional-hazards model for analysis.

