### Outcome measurements

#### Efficacy indicators

The primary outcome is the changes in the COPD assessment test (CAT) score after 52-week of treatment. Specifically, the differences between the total CAT score at week 52 and baseline will be calculated respectively for the experimental and the control groups, respectively, and the difference between the two groups will be compared. The secondary outcomes include the following eleven indicators:Annualized rates of moderate or severe COPD exacerbations. The measure is the number of acute exacerbations of moderate or severe COPD during 52-week treatment/total participants in the group. The definition of an acute exacerbation of COPD (AECOPD): is an acute change in a patient’s baseline dyspnea, cough, and/or sputum beyond day-to-day variability sufficient to warrant a change in therapy. The severity of AECOPD is graded as follows: (1) Mild: requires only increased treatment with short-acting bronchodilators, such as short-acting β-receptor agonists (SABA); (2) Moderate: requires increased antibiotics and/or oral glucocorticoid hormone; (3) Severe: requires hospitalization or emergency treatment, may be complicated by acute respiratory failure.All-cause admission rate and admission rate due to acute exacerbation. All-cause admission rate = (total number of admission during 52-week treatment)/ (total number of participants in the group) and the admission rate due to acute exacerbation = (number of admission due to acute exacerbation during 52-week treatment)/ (total number of participants in the group).The changes in the St George's Respiratory Questionnaire (SGRQ) score.The proportion of patients with an SGRQ response (defined as an improvement of ≥ 4 units from baseline).The changes in the CAT score.The median time to the first exacerbation of COPD and the median time to the first exacerbation of moderate or severe COPD during treatment.Duration and time interval of acute exacerbations compared with the control group.Annualized rates of acute exacerbations of COPD of different severity.The changes in clinical symptom score (Table 2) compared with the control group.The changes in the individual clinical symptom score compared with the control group.Frequency of first-aid drug use.The changes in TCM constitution from the baseline to week 24 and week 52.

**Table 2 Tab2:** The clinical symptom assessment scale

Item	Symptoms Assessment rating scale			
	0 (none)	1 (mild)	2 (moderate)	3 (severe)

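### Fisher's exact test is prescribed for exacerbation and admission rates that the protocol defines as events per participant; it does not test an event rate, and a count model should replace it

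*Protocol article*

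**What the plan says.** Under Outcome measurements (Efficacy indicators), the first secondary outcome, the annualised rate of moderate or severe exacerbations, is "the number of acute exacerbations of moderate or severe COPD during 52-week treatment/total participants in the group". The admission outcomes have the same form: "All-cause admission rate = (total number of admission during 52-week treatment)/ (total number of participants in the group", and likewise for admissions due to exacerbation. Rates by exacerbation severity are a further outcome. First-aid drug use appears only as "Frequency of first-aid drug use", with no definition.

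Under Statistical analysis (Efficacy analysis), Fisher's "exact test will be used to compare categorical variables, including the annualized rates of moderate or severe COPD exacerbations". The list continues with "all-cause admission rate, admission rate due to acute exacerbation, the proportion of patients with an SGRQ response", the severity-specific exacerbation rates, "and the frequency of first-aid drug use". No count model is named for any of these, and no rule says how a rate becomes a contingency table.

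**The concern.** The numerators count events, not patients, and nothing bounds the ratio at 1. Fisher's exact test needs independent units, each in one cell of a table. Of the outcomes in the list, only SGRQ response clearly has that form.

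Exacerbation reduction is the first-listed secondary outcome, the reported result of the team's earlier trial (Background), and one of the two management goals named in the Discussion. As written, its p-value depends on a table that the analyst must devise. The article also has the statistical analysis done after unblinding, so an unsettled choice of table could be made with the groups known.

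The outcome is called annualised, yet its denominator is participants rather than person-time. The Sample size section allows 20% attrition, and the withdrawal section lists several routes out of the trial. A contingency-table test cannot adjust for unequal follow-up.

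**Working it through.** **The plan's own figure.** The article states no rate, dispersion or power for the event outcomes, so there is nothing of that kind to reproduce. The only sample size is for CAT: 2 × (1.96 + 0.8416)² × 6.2184² / 2.2² = 125.4, so 126 per arm and 252 in total; 126 / 0.8 = 157.5, so 158 per arm and 316 in total. Both stated totals reproduce.

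**Inputs.** From the article: 158 per arm randomised, 126 per arm after attrition, two-sided 0.05. Assumed: event rate λ per participant over 52 weeks, and negative binomial dispersion k = 0 (Poisson), 0.5 or 1, giving a variance of λ + kλ² per patient. Each null scenario was simulated 5,000 times.

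**Reading 1: events against participants minus events.** The table treats an arm's rate as a binomial proportion with variance λ(1 − λ)/n. Its true variance is (λ + kλ²)/n, which is larger by the factor (1 + kλ)/(1 − λ). The large-sample rejection rate is therefore 2[1 − Φ(1.96/√factor)]. At λ = 0.5, k = 0 the factor is 1/0.5 = 2, and 1.96/1.414 = 1.386 gives 16.6%. At λ = 0.5, k = 1 it is 1.5/0.5 = 3, and 1.96/1.732 = 1.132 gives 25.8%. Fisher's test is conservative, so the simulated values are somewhat lower.

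All values are percentages under no treatment effect, 158 per arm, for k = 0 / 0.5 / 1:

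| λ | Simulated rejection | Large-sample formula | Table impossible |
|---|---|---|---|
| 0.1 | 4.2 / 4.6 / 5.4 | 6.3 / 7.0 / 7.6 | 0 |
| 0.2 | 5.5 / 7.3 / 8.4 | 8.0 / 9.5 / 11.0 | 0 |
| 0.3 | 8.1 / 10.8 / 13.1 | 10.1 / 12.6 / 15.0 | 0 |
| 0.5 | 14.0 / 19.0 / 23.4 | 16.6 / 21.5 / 25.8 | 0 |
| 0.7 | 26.5 / 33.2 / 39.3 | 28.3 / 35.6 / 41.0 | 0 / 0 / 0.1 |
| 0.9 | 44.0 / 48.1 / 49.2 (of tables that can be formed) | 53.5 / 60.7 / 65.3 | 17.6 / 24.9 / 29.0 |
| 1.0 | 39.1 / 42.3 / 48.2 (of tables that can be formed) | – | 72.8 / 72.5 / 73.3 |
| 1.2 | – | – | 100 / 99.9 / 99.7 |

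A table is impossible when either arm has more events than participants. At λ = 1.2, for instance, 158 × 1.2 is about 190 events, and the no-event cell would be 158 − 190 = −32. At λ = 1.0 one arm exceeds 158 events with probability about 48%, so at least one arm does with probability 1 − 0.52² = 73%. Allowing for simulation error, the ranges are about 4–9% rejection at λ = 0.1–0.2 and about 16–30% impossible tables at λ = 0.9. Results at 126 per arm are similar.

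**Reading 2: ever against never had an event.** Type I error was 1.7–4.2% in all scenarios, so there is no inflation. The quantity tested is now a proportion, and the contrast shrinks. With a control rate of 1.0 and an assumed rate ratio of 0.677 (the earlier trial's 32.3% risk reduction, borrowed as a rate ratio), the Poisson proportions with any event are 1 − e^(−1) = 0.632 and 1 − e^(−0.677) = 0.492. A 32.3% reduction in rate becomes 1 − 0.492/0.632 = 22%.

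Power in % at 126 per arm, k = 0 / 0.5 / 1:

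| Control rate | Ever/never Fisher | Comparison of mean rates |
|---|---|---|
| 0.5 | 38 / 31 / 24 | 50 / 44 / 37 |
| 1.0 | 56 / 39 / 30 | 80 / 66 / 56 |
| 1.5 | 64 / 41 / 28 | 93 / 77 / 64 |

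The mean-rate comparison uses a between-patient variance, as a simple stand-in for a count model. It held type I error at 4.2–5.5% in every scenario.

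**The case against.** The article does not describe the table of events against participants minus events, and Fisher's test is not confined to two-by-two tables. Patients could be classed by number of events (0, 1, 2, 3 or more). In a simulation of that version at 158 per arm, with a chi-square approximation to the exact test, null rejection was 4.3–5.3%. Power at a rate ratio of 0.677 and a control rate of 1.0 was 74 / 57 / 43% for k = 0 / 0.5 / 1. So a valid and computable use of the test exists, with most of the repeat-event information kept. This stands, but that version still compares distributions over categories, gives no rate ratio and ignores follow-up time.

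A reader might infer that the plan as written is infeasible or inflates type I error several-fold for all these outcomes. The documents do not support that. Both harms belong to one way of building the table and to moderate or high rates. The article gives no expected rate. Its entry criterion of at least two moderate or one severe exacerbation in the past year makes such rates plausible for exacerbations, but admissions or severe events could lie at 0.1–0.2, where inflation is small.

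A reader might also take first-aid drug use to be a count. The article never says so; if it means the proportion of users, Fisher's test is suitable.

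That an article condenses a fuller plan does not answer the core point. The article names both the test and the outcomes, so this is a stated mismatch and not an omission.

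**Conclusion.** The point holds in a conditional form. The definitions and the prescribed test do not fit each other for the moderate/severe exacerbation rate and the two admission rates, nor for the severity-specific exacerbation rates. That needs no assumption.

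The size of the harm does rest on assumed rates and dispersion. Under the literal table, type I error is about 4–9% at 0.1–0.2 events per patient, 14–23% at 0.5 and 27–39% at 0.7. The table cannot be formed in about 16–30% of trials at 0.9, 73% at 1.0 and over 99% at 1.2. Under ever/never, type I error is controlled, but the defined rate goes untested and power falls, for example to 30–56% from 56–80% at a control rate of 1.0. That comparison also assumes that the earlier trial's risk reduction can be read as a rate ratio.

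This should be fixed, but it does not threaten the trial's main conclusion: every affected outcome is secondary, and the CAT sample size is unaffected.

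**What to change.** In Efficacy analysis, replace Fisher's exact test for the exacerbation rates (moderate/severe and by severity) and for both admission rates with a count model: negative binomial regression, or Poisson regression with robust variance. Include treatment and the eosinophil randomisation stratum as covariates and log follow-up time as offset, and report rate ratios with 95% confidence intervals. Keep Fisher's exact test for the SGRQ responder proportion.

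In Efficacy indicators, define first-aid drug frequency. If it is a count, use the same model; if it is the proportion of users, Fisher's test can stay.

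The cost is a wording change and a standard model in the planned SAS software, with no new data. Make the change before database lock and unblinding.

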### Sample size

According to the results of the previous study [15], the mean difference in CAT scores between the YPF group and the control group was 2.2, and the combined standard deviation was 6.2184. The sample size was calculated accordingly, with an α risk of 0.05 and a β risk of 0.2 in a two-sided contrast. This study required a minimum of 252 subjects. Allowing for 20% attrition, a total sample size of 316 subjects was required, 158 in the treatment group and 158 in the control group.

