### Randomization, blinding and unblinding

The Interactive Web Response System (IWRS) will be used in this study. We will perform stratified block randomization for the eligible subjects, the absolute value of eosinophils in peripheral blood at the time of enrollment is taken as the stratification factor, and the cut-off value of the absolute value of eosinophils is set at 0.3 × 10^9^/L. The SAS 9.4 is used to generate the random number table and the drug random number table. Based on the two random number tables, the subjects are randomly divided into the YPF group and the control group. The administrator of IWRS will send the account number and password to the designated person in charge of each centre before the study. Then the investigator will log into the IWRS and enter the relevant information of the subject. The subject will be assigned a unique random number, which will be displayed by the IWRS.

In the trial, investigators, subjects, supervisors and clinical research coordinators will remain blinded. All experimental drugs and placebos are packaged in a uniform manner, with no difference in appearance, and blinded according to the drug random number table by people independent of the study. Investigators and subjects only know the random number and the drug number, and don’t know the treatment regimen represented by these random numbers.

Unblinding requirements: After all data have been entered into the Electronic Data Capture (EDC) system, the database is locked through a process of query, verification, and blinding review. The principal investigators and statisticians will then unblind the data and distinguish the groups of the subjects and corresponding interventions. The assessors then perform the statistical analysis after the data are unblinded. In case of an emergency (such as serious adverse events, serious complications, etc.) and the need for rescue measures, unblinding can be done urgently with the identification and signature of the principal investigator. The sponsor and the principal investigator should be notified within 24 h of the emergency unblinding, and the reason for the emergency unblinding should be explained. The rate of emergency unblinding should not exceed 20%, otherwise, the study may be considered a failure. Unblinding should not be performed in cases of withdrawal for therapeutic reasons.

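### Fisher's exact test for SGRQ response is valid but conservative, and gives up a few points of power that a test stratified by eosinophils would recover

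*Protocol article*

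**What the plan says.** In the protocol article, Efficacy indicators lists this secondary outcome: "The proportion of patients with an SGRQ response (defined as an improvement of ≥ 4 units from baseline". Each patient either responds or does not, so the outcome is binary.

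Efficacy analysis states that Fisher's "exact test will be used to compare categorical variables", and the list that follows includes "the proportion of patients with an SGRQ response". No stratification is mentioned for that test. The general Statistical analysis paragraph sets the level: "All analyses will be two-sided, with a" p-value threshold of 0.05.

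Three other places bear on the choice:

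- Randomization, blinding and unblinding says that "the absolute value of eosinophils in peripheral blood at the time of enrollment is taken as the stratification factor", with a cut-off of 0.3 × 10^9/L.
- Subgroup analyses plans a stratified analysis of the efficacy indicators by eosinophils.
- Demographic and baseline analysis and Safety analyses both allow either the chi-square test or Fisher's test. For adverse events, the chi-square test or Fisher's "exact test will be used to compare the incidence of AEs among groups".

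**The concern.** Fisher's test conditions on both margins of the two-by-two table. Its p-value can take only a limited set of values, so its true error rate lies below the nominal 5%. That is a fair price when cells are small and the large-sample approximation is in doubt. Here the arms are large. Even at a pooled response rate of 20%, the smallest expected cell with 126 per arm is 126 × 0.20 = 25.2. An expected count below 5 would need a pooled rate below 5/126 = 4.0%, or above 96.0%.

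The plan therefore pays for a protection that it is unlikely to need. The trial is sized on the CAT score alone, so power for SGRQ response is not assured. The overall test also leaves out the factor that the randomisation is stratified on.

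**Working it through.** **Arm sizes.** Sample size states that the CAT difference "was 2.2, and the combined standard deviation was 6.2184", "with an α risk of 0.05 and a β risk of 0.2 in a two-sided contrast". The usual formula for two means gives

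n per arm = 2 × (1.960 + 0.842)² × 6.2184² / 2.2² = 125.4, rounded up to 126, or 252 in total.

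With 20% attrition, 126 / 0.8 = 157.5, rounded up to 158 per arm, or 316 in total. Both stated figures reproduce. SGRQ response will be analysed on somewhere between 126 and 158 patients per arm, depending on attrition and how it is handled.

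**Method.** For each arm size, list every possible pair of responder counts (a, b). Mark whether two-sided Fisher gives p < 0.05 and whether the uncorrected Pearson chi-square does. The rejection probability is the sum, over the marked pairs, of Bin(a; n, p₁) × Bin(b; n, p₂). Setting p₁ = p₂ gives the true error rate; p₁ ≠ p₂ gives power. The response rates are assumptions, because the protocol gives none.

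**True two-sided error rate at nominal 5%**

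| Response rate, both arms | Fisher, 126 | Chi-square, 126 | Fisher, 158 | Chi-square, 158 |
|---|---|---|---|---|
| 20% | 3.5% | 4.9% | 3.6% | 4.9% |
| 30% | 3.7% | 5.0% | 3.8% | 5.0% |
| 40% | 3.6% | 4.8% | 3.8% | 5.0% |
| 50% | 3.7% | 5.1% | 3.7% | 4.9% |

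The highest Fisher value found between 20% and 60% is 3.9% (rate 35%, 158 per arm). At a rate of 10%, Fisher falls to 2.9% (126 per arm) and 3.2% (158 per arm).

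**Power for two assumed pairs of rates**

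| Control v YPF | Per arm | Fisher | Chi-square | Loss (points) |
|---|---|---|---|---|
| 40% v 55% | 126 | 62.1% | 66.9% | 4.7 |
| 40% v 55% | 158 | 72.4% | 76.1% | 3.7 |
| 30% v 45% | 126 | 64.7% | 69.2% | 4.5 |
| 30% v 45% | 158 | 76.0% | 79.4% | 3.4 |

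Losses are taken before rounding.

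**Range of the loss, assumed control rates 20% to 50%**

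| Difference between arms | 126 per arm | 158 per arm |
|---|---|---|
| 10 to 15 points | 4.3 to 5.4 | 2.9 to 4.9 |
| 20 points | 1.8 to 2.5 | 0.8 to 1.4 |
| 25 points | under 1 | under 1 |

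**What the stratum adds.** A Cochran-Mantel-Haenszel (CMH) test was simulated, assuming 30% of patients in the high-eosinophil stratum and response rates that differ by 0, 10 or 20 points between strata. Its error rate is 4.8% to 5.1%. For 40% v 55%, its power is 66.7% to 67.6% at 126 per arm and 76.0% to 77.3% at 158. Against an unstratified chi-square under the same conditions, it gains about 0 to 1.8 points. Nearly all of the loss therefore comes from the exact test, and little from leaving out the stratum.

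**The case against.** The strongest objection is that nothing here is wrong. Fisher's test is valid at any sample size and keeps the 5% limit, and no conclusion drawn from it would be unsound. That stands. This is an efficiency point, and the protocol claims no power for SGRQ response.

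A fixed power loss might be read into this. The documents do not support one: without a response rate, the loss can be anywhere from about 0 to 5 points, and it shrinks quickly once the arms differ by 20 points or more.

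A reader might also infer any of the following:

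- **No effect size will be estimated.** The article does not say so. It is silent, and a condensed article may leave effect measures for secondary outcomes to the full protocol or the analysis plan.
- **Eosinophils are ignored.** Subgroup analyses does plan a stratified analysis of the efficacy indicators. It sits among the subgroups, though, and does not clearly supply an adjusted overall test.
- **The efficacy section contradicts the baseline and safety sections.** Those allow chi-square or Fisher's test, so naming one of the two is not a contradiction.
- **The responder proportion is meant to confirm the CAT result.** The Discussion hopes for mutual confirmation from the clinical symptoms and the SGRQ scores. It does not mention the responder proportion.

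What survives the objection is that the article names the test, so this is not a detail left open, and that a better choice costs nothing.

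**Conclusion.** The point holds as a minor one. The test named for SGRQ response runs at a true level of about 3.5% to 3.9% where chi-square would use close to the full 5%, and it makes no use of the randomisation stratum in the overall comparison. The cost is a few points of power for moderate differences and almost nothing for large ones. This rests on assumed response rates of 20% to 60%, on 126 to 158 analysed patients per arm and, for the stratified test, on an assumed 30% of patients in the high-eosinophil stratum. The validity of the trial and the primary CAT conclusion are not affected.

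**What to change.** In Efficacy analysis, take SGRQ response off the Fisher list and add one sentence: the proportions will be compared with a CMH test stratified by the eosinophil stratum used at randomisation (cut-off 0.3 × 10^9/L), reported with the stratum-adjusted risk difference and its 95% confidence interval, and Fisher's exact test will be used only if an expected cell count is below 5. Settle this before unblinding. If the analysis plan already specifies such a test, it is enough to bring the article's wording into line.

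The cost is that sentence. No new data and no change to trial conduct are needed. CMH is a large-sample test, but at these arm sizes its simulated error rate stays at 4.8% to 5.1%. If a stratified test is not wanted, a plain chi-square test would still recover nearly all of the lost power.
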